## Abstract

**Introduction:**

There are great potential benefits of being able to conduct neuropsychological assessments remotely, especially for hard-to-reach or less mobile patient groups. Such tools need to be equivalent to standard tests done in the clinic and also easy to use in a variety of clinical populations.

**Methods and analysis:**

This study protocol describes a cross-sectional study aimed at validating the newly developed digitalized neuropsychological test battery Mindmore Remote in patients with neurological disorders and injuries. Diagnoses comprise traumatic brain injury, stroke, Parkinson’s disease, multiple sclerosis, brain tumour and epilepsy. 50 patients in each patient group will be included. In addition, 50 healthy controls will be recruited. All participants will undergo both testing with Mindmore Remote at home and traditional neuropsychological assessment face-to-face in a randomised order. The primary outcome is the association between tests from the Mindmore Remote battery and their equivalent traditional neuropsychological tests. Further, bias between methods and differences between groups will also be investigated.

**Ethics and dissemination:**

The study protocol has been approved by the Swedish Ethical Review Authority (2022-06230-01) and adheres to the declaration of Helsinki. All participants will be given oral and written information about the study and sign informed consent forms before entering the study. All participants are informed that they can terminate their participation in the study at any given time, without giving any explanation, and participating in the study or not will not affect their care at the clinic. Neither authors nor personnel involved in the research project are affiliated with Mindmore AB. The results from the study will be published in peer-reviewed scientific journals and presented at national and international conferences on the topic.

**Trial registration number:**

NCT05819008.

STRENGTHS AND LIMITATIONS OF THIS STUDYA large cross-sectional study including 300 patients with different neurological disorders and injuries, and 50 healthy controls.The patients are clinical patients currently being under evaluation for cognitive deficits, making the results from the study clinically generalizable.If the remote test battery proves to be valid, such results would have direct practical implications in clinical practice.Excluding participants with languages and cultural backgrounds other than Swedish limits the generalizability of the findings to the entire Swedish population.

## Introduction

Digital meetings are now a ubiquitous part of everyday life in many parts of the world, not least following the COVID-19 pandemic that necessitated widespread use of methods for online communication. These developments have the potential to benefit healthcare in situations where physical meetings are challenging. Remote healthcare solutions have always been a pertinent issue for patients from sparsely populated areas, who have a high degree of motor and/or cognitive disability, or who have difficulties or lack the resources to travel.

Patients with neurological conditions are a highlighted group in this regard. Due to injuries or progressive diseases within the central nervous system, they often struggle with logistical problems, either directly or indirectly related to their physical and mental symptoms. Diagnoses include traumatic brain injury,^1 2^ stroke,^3^ Parkinson’s disease,^4^ multiple sclerosis,^5^ epilepsy^6^ and brain tumours.^7^ These conditions result in structural and functional disruptions to the brain and/or spine, causing both physical and cognitive disabilities. Deficits in cognitive and executive functioning are among the most common symptoms in patient groups. These characteristics render neuropsychological assessment a key part both in diagnosis and rehabilitation.^8^

Traditionally, the neuropsychological examination requires a physical meeting. The psychologist records the performance of the patient using paper-pencil test and a manual stopwatch. After the testing session, the psychologist manually scores the tests and compares the outcomes to normative performance using tables from testing manuals or peer-reviewed research articles. This is a time-consuming endeavour, with high costs for both patients and the healthcare system.

Computerised testing has become more common in the 21st century,^9 10^ including combinations of paper-pencil tests and computers or tablets.^11 12^ This has reduced the time that psychologists spend scoring results from neuropsychological tests. Traditional testing nevertheless requires the patient to physically visit a clinic for the assessment. During the last few years, there has been an increasing interest in performing neuropsychological assessment remotely.^13^

A core problem is that neuropsychological assessments are difficult to adapt to a digital, remote platform. Standardisation is a necessary component in many tests (see, eg, Delis *et al*
14 or Wechsler^15 16^) since results are compared with a normative population who have performed the tasks under the same conditions. Changing the administration procedure too much might make the results invalid. While some traditional tests such as simple verbal tasks may be administrated through, eg, video conference without major threats to validity, other tasks such as those requiring motor responses or visual tracking are ill-suited for such solutions.^17 18^ There are some examples of neuropsychological testing platforms that also include automated administration and scoring procedures, such as Test My Brain Digital Neuropsychology Toolkit,^19^ Philips IntelliSpace Cognition^20^ or the Cogniciti’s Brain Health Assessment.^21^ It is, however, necessary to thoroughly validate such tools before they can be implemented in healthcare.

Mindmore (www.mindmore.com) is an automated digital application originally distributed to patients on-site at a clinic or healthcare provider using a tablet device. Its constituent tests have been validated in healthy adults^11^ and include normative data scores.^22^ A remote version (Mindmore Remote) is currently under development so that patients can complete neuropsychological testing procedures at home without any healthcare personnel present. Mindmore Remote is currently undergoing validation, and normative data are being collected from healthy adults ([name], personal communication, approved ethics application by the Swedish Ethical Review Authority, dnr 2019-02030). However, the instrument does currently not include data from patient groups with cognitive impairments. This protocol presents a research project aiming to validate Mindmore Remote in patients with neurological disorders and injuries.

### Objectives

The primary aim of this project is to assess the convergent validity of Mindmore Remote tests by comparing them with standardised neuropsychological tests. We pose the following research questions:

Are the tests in Mindmore Remote equivalent to traditional neuropsychological tests in patients with traumatic brain injury, stroke, multiple sclerosis, Parkinson’s disease, epilepsy and brain tumour?Can the results from Mindmore Remote be transferred into neuropsychological profiles (eg, the distribution of performance across several tests) that can be used for patients with Parkinson’s disease and Multiple Sclerosis?How do the patients experience undergoing a neuropsychological evaluation on their own compared with traditional neuropsychological assessment in a physical meeting with a psychologist?

## Methods and analysis

### Study design and setting

This study is a cross-sectional study with a case-control design. All reporting of results in peer-reviewed scientific journals will adhere to the STROBE guidelines.^23^ The study is located at the Neuro-Head-Neck Centre (NHHC), including the departments of Neurology, Neurosurgery and Neurorehabilitation at Umeå University Hospital, Umeå. Data collection will be conducted during March 2023–December 2025.

### Participants

Patients with diagnoses of traumatic brain injury, stroke, Parkinson’s disease, multiple sclerosis, epilepsy and glioma who are referred for neuropsychological assessment at NHHC will be offered to participate in the study. The aim is to include 50 patients in each diagnostic group.

Healthy adults (*n*=50) will be recruited as controls through advertising at Umeå University Hospital. Since the patient groups will differ in age variance, the aim is to recruit a control group with a variance in age. The controls will be reimbursed for their participation (100 SEK; approximately €10).

### Eligibility criteria

The inclusion and exclusion criteria are the same for patients and healthy controls, except that healthy controls should not be diagnosed with any neurological disorders.

#### Inclusion criteria

Physician-generated neurological diagnosis of either traumatic brain injury, stroke, Parkinson’s disease, multiple sclerosis, epilepsy and glioma.Age 18 or aboveIn possession of a computer with internet connection.

#### Exclusion criteria

Any other neurological diagnosis than the primary diagnosis (for healthy controls, any neurological diagnosis).Severe psychiatric disorders, including schizophrenia or other psychotic disorders, severe depression, bipolar disorder and suicidality.Addiction disorder, including both alcohol and other substances.Not speaking Swedish, have lived in Sweden less than 10 years and/or have had a majority of education outside of the Swedish educational system.Not being able to participate in a neuropsychological examination, or to give informed consent due to physical or mental disability.

### Instruments

#### Primary outcome measures: neuropsychological tests

All participants will be tested using all tests in the Mindmore Remote battery and corresponding traditional neuropsychological tests. Table 1 summarises all tests in Mindmore Remote and provides a detailed description of each test, primary outcome measures and the corresponding traditional neuropsychological test that will be used to test the validity of each Mindmore Remote test. The test battery will be performed in the order given in table 1, with the addition that the RAVLT Retention and Recognition trials will be performed after Stroop in the Mindmore Remote battery, and Word List Recall and Recognition Trials will be performed after Color-Word-Interference Test in the traditional battery.

**Table 1 T1:** Outcome measures

Mindmore Remote test	Description	Main outcomes	Validity test
Symbol Digit Processing Test (SDPT)	SDPT is a test of attention and mental processing speed. The participant views a digit-symbol code key on the top of the screen. In the middle of the screen, one symbol appears. The task is to press the correct number as quickly as possible using the mouse on a number pad at the bottom of the screen.	Number of correct items coded over 90 seconds.	Coding from WAIS-IV (Wechsler, 2008)
Rey Auditory Verbal Learning Test (RAVLT)	RAVLT is a test of verbal learning and episodic memory. The participant will hear 15 words presented over five trials, with a recall task after each trial. After the learning trial, a distraction list of 15 words is administered, and after this, the task is to recall the first list once again. After 30 minutes (after Stroop below), a free recall retention trial is performed, and after this, a recognition trial, where the participant is supposed to identify the words of the first list in a list of 15 hits and 15 distractors. All responses are given verbally.	Total Learning—Number of words recalled during all five trials; Short-term Recall—Number of words recalled after the distraction list; Long-term recall—Number of words recalled after 30 minutes; Recognition—Number of correct hits and true negatives during recognition.	Word List Recall I and II from WMS-III^15^
Corsi Block	Corsi Block is a test of short-term and working memory. On the screen, 10 white squares will appear. These will blink in yellow in specific sequences of increasing length, starting with two items. Two different sequences will be presented of each length. After each sequence has finished, the participant is supposed to click with the mouse on the squares in the same order (Corsi Forwards) or in reverse order (Corsi Backwards). If the participant fails to produce the correct sequence in both trials on the same level, the test will end. Corsi Forwards is performed first and then Corsi Backwards.	Corsi Block Forwards—Number of correct trials in the forward condition; Corsi Block Backwards—Number of correct trials in the Backward condition.	Block Span from WMS-III^15^
Trail Making Test (TMT) – Click	TMT is a test of attention, visuomotor speed and the executive function of switching. The test consists of three conditions. In condition 1 (Number Sequencing), the participant will see numbers 1–25 in small circles on the screen and is supposed to click on the numbers in the correct order. In condition 2 (Switching), both numbers 1–13 and letters A–M appear in the circles. The participant is supposed to click on the letters and numbers in order, but each number and letter interchangeably – 1-A-2-B-3, etc. In condition 3 (Motor Speed), the circles are connected by a dotted line, and the participant is instructed to click on the circle in the same order as the line connects them.	Time to completion of each trial.	Trail Making Test from D-KEFS^14^
Stroop	Stroop is a test of the executive function inhibition, performed in two conditions. In condition 1 (Colour Naming and Reading), a colour word appears, printed in the same colour. The participant is instructed to click as quickly as possible on the correct colour word (blue, red, green or yellow), spelt out in black colour below the target word. In condition 2 (Inhibition), the colour words are written in a different colour. The participant is instructed to click, as quickly as possible, on the colour word written in black colour below the target word that matches the colour of the word, and not the word in itself.	Time to completion of each trial.	Color-Word Interference Test from D-KEFS^14^
FAS	In FAS, a test of verbal production and executive functions, the participant is instructed to say as many words as possible during 1 min, starting with a specific letter. The test is performed in three trials using letters F, A and S, respectively.	Number of words produced over all trials.	Verbal Fluency from D-KEFS^14^

All tests will be performed using Swedish versions.

D-KEFS, Delis-Kaplan Executive Functions System; WAIS, Wechsler Adult Intelligence Scale; WMS, Wechsler Memory Scale.

Raw scores of the tests will be used as the main variables in the analyses. However, scaled scores (ie, those computed from the normative samples in the test manuals of the traditional tests and from the built-in norms in Mindmore Remote) might also be considered in some analyses.

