### Data analysis plan

Validation of Mindmore test against traditional paper-pencil neuropsychological test will be performed using Pearson and/or Spearman correlation coefficients depending on the distribution of data. To evaluate bias between methods, the Bland-Altman method^25^ will be used. In addition, multiple linear regressions will be performed to investigate and adjust for the influence of background variables, such as age, education, gender, diagnosis and time since injury/diagnosis. To establish neuropsychological profiles of diagnostic groups, descriptive data from each test will be presented, and analysis of variance, with and without covariates, will be performed to determine differences between groups. Due to multiple statistical analyses, adjustments for multiple comparisons will be considered.

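### With raw scores as the default and no other scale named for Bland-Altman, the method bias would mix scale differences with real bias for test pairs whose raw metrics differ

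*Protocol article*

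**What the plan says.** All references are to the protocol article.

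- **Score scale.** The text below Table 1 (Primary outcome measures: neuropsychological tests) sets a general default: "Raw scores of the tests will be used as the main variables in the analyses". Scaled scores are mentioned as an option that "might also be considered in some analyses"; those analyses are not named. Each battery would be scaled from its own source, and the article describes such scores as "those computed from the normative samples in the test manuals of the traditional tests and from the built-in norms in Mindmore Remote".
- **Agreement method.** The Data analysis plan has the words "To evaluate bias between methods, the Bland-Altman method" and gives no score scale for that analysis. No other agreement method is named.
- **Question served.** The first research question under Objectives begins "Are the tests in Mindmore Remote equivalent to traditional neuropsychological tests in patients with" and goes on to list the six diagnoses.
- **Pairs.** Table 1 sets each remote test against a traditional one. SDPT, scored as "Number of correct items coded over 90 seconds" with mouse responses, is set against "Coding from WAIS-IV". RAVLT (15 words, five trials) is set against the WMS-III word list, Corsi Block (10 squares, clicked) against WMS-III Block Span, and TMT-Click against the D-KEFS Trail Making Test. A click Stroop is set against D-KEFS Color-Word Interference, and FAS against D-KEFS Verbal Fluency. Item counts, durations and maximum scores are given for remote tests only.

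**The concern.** A Bland-Altman mean difference is a method bias only if both methods report the same quantity in the same unit. Table 1 does not pair two administrations of one test. Four of the six remote tests (SDPT, Corsi, TMT, Stroop) are answered by clicking, while the Introduction and Data analysis plan describe the traditional tests as paper-pencil with a manual stopwatch. Several pairs are also differently named instruments, and each battery has its own norms.

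If the raw metrics of a pair differ, a non-zero raw difference is expected even when both tests grade every patient alike. Unequal raw SDs also make the difference rise or fall with the mean, which looks like proportional bias. This matters for the equivalence question. Correlation ignores shift and scale, so Bland-Altman is the only named analysis that could detect a systematic difference between methods.

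**Working it through.** **The plan's own figures.** The protocol gives no figure for Bland-Altman. Its only computed figures are in Sample size and concern differences between groups. They reproduce with a two-sided normal approximation: n = 2(1.96 + 0.84)²/1² = 15.7, so 16 per group. With 50 per group, power is 0.9988 at 1 SD (stated 0.999) and 0.705 at 0.5 SD (stated 0.706). Nothing below depends on them.

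**Step 1: perfect correlation.** Let the raw SDs differ by a ratio k > 1 and let r = 1. The SD of the difference is (k − 1) times the smaller SD, so the limits are the mean difference ± 1.96(k − 1) smaller SDs:

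- k = 1.2: 1.96 × 0.20 = 0.39 SD
- k = 1.33: 1.96 × 0.33 = 0.65 SD
- k = 1.5: 1.96 × 0.50 = 0.98 SD

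On a common scale all three would be 0. The values of k are assumptions, because the document gives no raw ranges or SDs for the comparators.

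**Step 2: imperfect correlation.** Assume the remote test has mean 50 and SD 10, and the comparator has mean 50k and SD 10k, with correlation ρ and no true bias once the scale is removed. Then:

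- mean difference = 50(k − 1)
- half-width of limits = 1.96 × 10 × √(1 + k² − 2ρk)
- correlation of difference with mean = (k² − 1)/√[(1 + k² − 2ρk)(1 + k² + 2ρk)]

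| ρ | k | Raw mean difference | Raw half-width | Common-scale half-width | Correlation of difference with mean |
|---|---|---|---|---|---|
| 1.0 | 0.75 | −12.5 | 4.9 | 0 | −1.00 |
| 1.0 | 1.33 | +16.5 | 6.5 | 0 | +1.00 |
| 0.8 | 0.75 | −12.5 | 11.8 | 12.4 | −0.44 |
| 0.8 | 1.33 | +16.5 | 15.7 | 12.4 | +0.43 |
| 0.7 | 0.75 | −12.5 | 14.0 | 15.2 | −0.38 |
| 0.7 | 1.33 | +16.5 | 18.7 | 15.2 | +0.38 |

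The raw mean difference and the slope arise from scale alone. On the common scale both are zero.

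**Step 3: how much of the width is scale.** The variance factor splits as 1 + k² − 2ρk = (k − 1)² + 2k(1 − ρ). The first term is scale and the second is imperfect agreement. At ρ = 0.8 and k = 1.33 they are 0.109 and 0.532, so scale is 0.109/0.641 = 17% of the variance. At ρ = 0.7 and k = 1.33 they are 0.109 and 0.798, so scale is 0.109/0.907 = 12%. At these correlations, most of the width is real disagreement. Scale chiefly displaces the limits and adds the slope.

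**Step 4: the primary analysis.** Pearson's coefficient is unchanged by a positive linear rescaling and Spearman's by any increasing one. Neither is touched by this point.

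**The case against.** Four stronger readings are tempting, and the document does not support them.

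- **That Bland-Altman is prescribed on raw scores.** No sentence says so. It follows from the general default, and scaled scores stay open. The scale of a secondary analysis could be settled in a fuller plan that is not shown. This stands as a limit on the wording. However, the article does state a default, and that default is unsuitable for one of its named methods.
- **That units or test lengths are shown to differ.** The comparators are named without item counts, durations or scoring. FAS with Verbal Fluency (words) and the two Trail Making tests (seconds) may share units. What the text shows is differently named instruments and different response modes.
- **That the limits reflect scale and not disagreement.** This is true only at r = 1. Step 3 shows the reverse at correlations of 0.7 to 0.8.
- **That the primary outcome is compromised.** It is not. The Abstract defines the primary outcome as association and places bias among the further analyses.

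Two more arguments deserve weight. First, a raw shift is informative if one asks whether traditional norms could be applied directly to a remote score. That is a narrower question than equivalence, and Mindmore Remote is described as having its own norms. Second, scaled scores might already be the answer. The Introduction says that "normative data are being collected from healthy adults" for the remote version, but the text below Table 1 mentions built-in norms and data collection runs to December 2025. Nothing shows that norms will be unavailable at analysis. Still, such scores rest on two separate norm sets, and a difference between those samples would appear as method bias.

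**Conclusion.** The point holds in a limited form. Followed as written, the raw-score default would give Bland-Altman results in which the mean difference, and any trend with the mean, cannot be read as method bias for pairs whose raw metrics differ. For those pairs the analysis would not answer the equivalence question. Which pairs are affected, and by how much, cannot be established from the document. The limits of ±0.39 to ±0.98 SD rest on assumed SD ratios of 1.2 to 1.5 and perfect correlation. The mean shifts of −12.5 to +16.5 points rest on an assumed mean of 50, an assumed SD of 10 and scale ratios of 0.75 to 1.33. Severity is moderate: the analysis is not primary, the correlations are unaffected, and no data would be lost.

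**What to change.** State the scale for each analysis in the Data analysis plan:

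- Keep raw scores for the correlations and regressions.
- Run Bland-Altman on a common metric, for example z-scores for both tests of a pair referenced to the study's own 50 healthy controls, who take both batteries. Add scaled scores as a sensitivity analysis.
- Use raw-score Bland-Altman only for pairs confirmed to have the same items, time limit and scoring unit, and list those pairs.

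The cost is wording only, since all the data are already to be collected. Three downsides should be stated with the results:

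- Control-referenced z-scores set the mean bias in controls to zero. They show whether a patient's deficit is the same size under both methods, but not a shift common to everyone.
- The control SD carries sampling error of about 1/√(2 × 49) = 10% at n = 50.
- Scaled scores depend on two separate norm sets, which can add a bias of their own.
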